#### Description of Questionnaires Used

##### PSS:NICU Questionnaire

The PSS:NICU was originally developed in 1993 [26]. It assesses neonatal intensive care unit–specific stressors on a Likert scale. Each item can be scored from 0 to 5, with a maximum total score of 230 over the 46 items. Modified versions exist, but the original full-length questionnaire will be used for this study as all subsections are of interest with changes to be implemented. 

##### GAD-7 Questionnaire

The GAD-7 is a 7-item self-administered questionnaire that assesses the presence and severity of symptoms of anxiety over the preceding fortnight. Scores range from 0 to 3 on each item, with a total score ranging from 0 to 21. There are established set points for mild, moderate, and severe anxiety [27].

##### PHQ-9 Questionnaire

The PHQ-9 is a 9-item self-administered questionnaire that assesses the presence and severity of symptoms of depression over the previous two weeks. It is scored in the same manner as the GAD-7 with total scores ranging from 0 to 27 and with established set points for mild, moderate, and severe symptoms [28].

### Washout Period, Phase 2 Preparation (4 Months)

A program to enhance father participation with the FICare model will be developed using the existing Neonatal DadPad or Imperial Family Delivered Neonatal Care app. Both of these apps are currently used in several NHS Trusts to guide fathers through their NU journey. The phase 1 and systematic review findings, along with guidance from the PAG will inform our decision for what is best suited for our local population.

Teaching sessions will be undertaken to educate and upskill all clinical NU staff on the study aims, recruitment, phase 1 study findings, and upcoming phase 2 study, highlighting the importance of fathers’ role in the FICare (eg, teaching parents how to safely give nasogastric feeds and nappy changes in a ventilated baby). In addition, there will be regular FICare teaching for staff, including encouragement of parents to attend ward rounds, and with guidance to parents in the workbook (Table 2).

**Table 2 table2:** Program to enhance father involvement in family integrated care.

Strategies	When	Who
Educational booklet or app, including Introduction to the neonatal unit Meeting the multidisciplinary team—tailored to the individual unit Family integrated care Taking care of yourselves Routine care and “observations” Breastfeeding Developmental care Medications Nutrition and growth Ventilation and breathing support Cardiac (heart) conditions Gastrointestinal and liver (gut) conditions Brain development Planning for discharge Eyes	At parents’ disposal	Both parents
Suggested tasks or workbook, including Kangaroo care Nappy changes in incubator Mouth care and cleaning of baby Reading of observations (heart rate, temperature, respiratory rate) Helping to weigh baby Bathing baby Ward round participation	To work through at parents’ pace	Both parents
Peer support sessions—led by specialist clinical psychologists or therapists	Every two weeks	Fathers^a,b^
Ward round participation	Daily	Both parents^a^
Bite-size education classes	2-3 per week at varying times including weekend	Both parents^a,b^

^a^Any parent in the unit is welcome to participate or attend.

^b^Sessions to occur at times to suit fathers with cultural, religious, family, and work obligations, as determined through phase 1 data collection.

### Phase 2 Study: Enhanced Father Involvement in FICare (9 Months)

Once a family is recruited, the program developed to enhance the father’s involvement in FICare will be implemented to take place at the parents’ pace (Table 2). Materials will be freely available to the study participants in a format suited to their needs (electronic or paper copy). All interested parents are encouraged to attend the peer support sessions, ward round participation, and bite-size education classes.

The NU experience and MH status of both parents will be assessed as in the phase 1 study (Figure 1) including assessing their experience of the FICare program. At the end of the phase 2 study, staff knowledge, experiences, and opinions about fathers and FICare will be reassessed and compared with the start of the study.

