### Study Design

This is a prospective, multicenter, and multiphase study. Phase 1 will assess baseline fathers’ experiences in the NU, their involvement in FICare, and MH status during babies’ NU admission up to 6 weeks postdischarge. Simultaneously, an SR of fathers’ involvement in FICare and their MH outcomes will be conducted. A program to enhance the involvement of fathers in FICare will be developed using information from the phase 1 study, SR, existing DadPad or Imperial Family Delivered Neonatal Care app, and advice from the parent advisory group (PAG). In the phase 2 study, an enhanced father involvement program in FICare will be implemented and similar assessments as in phase 1 will be conducted (Figure 1). We will provide regular debrief sessions, and research updates or newsletters to keep staff engaged and supportive of the project. This support will be continued throughout the study.

This study has been registered with clinicaltrials.gov (NCT06022991) [19].

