## Discussion

This study will test the hypothesis that if fathers are facilitated to engage more with their baby on the NU and are better supported during the neonatal stay, both parents will experience fewer MH symptoms during their baby’s hospitalization and up to 6 weeks postdischarge. Improving parents’ MH is shown to allow greater parent-child bonding [32] and more sensitive responsiveness of mothers to their infants’ cues [33]. Mothers engaged in the FICare model have greater confidence in caregiving at the point of discharge and seek less medical support after discharge [32]. It is anticipated that these results will translate to fathers or partners.

Unlike many other studies [12,33], this study includes parents of a wide gestational age range of premature infants, including extremely premature infants and those who are invasively ventilated and at the highest risk of adverse outcomes. This is vital as research has found that fathers find the fragile appearance of their premature infants causes significant stress [34]. A focus of the study methods will be to upskill NU staff to increase awareness and understand the importance of father engagement in FICare and their MH as well as the impact on mother and child, which is in line with the NHS Long Term Plan [17].

Limitations of the study include the need for conversational English. This is required to be able to complete the standardized questionnaires, participate in the interviews and focus groups, and to be able to engage with the phase 2 provisions. The language for the phase 2 materials will be kept as simple to ensure readability and understanding. Exclusion from recruitment based on language will be monitored. The perceived research burden may disproportionately impact parents who have older children, have a greater distance to travel, limited parental leave, or who do not have English as their first language. There may also be cultural barriers to overcome when discussing MH.

A prospective cohort study was the most practical and ethical study design. The sample size and the primary outcome of the study is based on the qualitative data. A bigger sample size will be required for the study to be based on the quantitative or questionnaire data. The quantitative or questionnaire data collected in this study is to support the qualitative data and to test the feasibility of collecting such data longitudinally.

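### The incentive to enrol differs between phases, because only phase 2 enrolment brings the booklet or app and workbook; differential volunteering is a possible confounder of the phase contrast, of unknown size and direction

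*Protocol article*

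**What the plan says.** **Phase 1.** Study Design says that "Phase 1 will assess baseline fathers’ experiences in the NU, their involvement in FICare, and MH status". The Overview of the phase 1 section lists what enrolment brings: questionnaires, two father interviews, focus groups for mothers, and contact after discharge. No programme is offered.

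**Phase 2.** The phase 2 section says: "Once a family is recruited, the program developed to enhance the father’s involvement in FICare will be implemented". On the materials it says: "Materials will be freely available to the study participants in a format suited to their needs".

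**Table 2.** Of the five strategies, peer support, ward rounds and classes carry footnote a: "Any parent in the unit is welcome to participate or attend". The booklet or app and the workbook do not. The phase 2 text makes the same division: "All interested parents are encouraged to attend the peer support sessions, ward round participation, and bite-size education classes".

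**Entry.** The text under Exclusion Criteria has every family in the gestation range assessed for eligibility and eligible parents recruited in sequence, up to 20 per phase. The father's or partner's own consent is required.

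**Timing.** The first questionnaires are completed within 7 days of recruitment. Phase 2 repeats the phase 1 assessments.

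**Monitoring.** The Discussion says: "Exclusion from recruitment based on language will be monitored".

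**The concern.** The study compares two successive groups of fathers, each of whom chose to take part. If what they are offered changes between the groups, the kind of father who accepts may change too. Someone keen to be involved, or someone in distress and looking for help, has a reason to consent in phase 2 that he did not have in phase 1.

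A phase difference could then exist before the programme has acted. This reaches the primary outcome as well as the scores, because paternal stress by interview comes from the same fathers as the questionnaires. It is a question of who enters, separate from any change over calendar time.

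The usual check would be to compare the phases at entry. That check is weak here: a phase 2 father may already have had the materials for some days when he completes the first questionnaires.

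**Working it through.** **1. Stated figure.** Sample Size gives 20 families per phase. With both parents, 20 × 2 = 40 per phase and 40 × 2 = 80 in total. Both reproduce. The article has no power calculation and no consent rate.

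**2. What enrolment changes in each phase**

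| | Phase 1 | Phase 2 |
|---|---|---|
| Assessments | on enrolment | on enrolment |
| Booklet or app, workbook | not offered | offered to participants |
| Peer support, ward rounds, classes (as programme elements) | not offered | open to any parent |
| Eligibility criteria | same | same |
| Father's consent | required | required |

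Only the second row differs in what enrolment brings: 2 of 5 strategies. The other 3 of 5 are available in phase 2 without joining.

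**3. Can the first scores separate selection from effect?** The programme starts on recruitment, and the questionnaires may be completed up to 7 days later. A phase difference in those scores could reflect who joined, early exposure, or both.

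**4. Scale, under assumptions.** Suppose willingness to join is normally distributed and correlates rho with the outcome, and that a proportion p1 consents in phase 1 and p2 in phase 2. The consenting group's mean is shifted by rho × m(p) SD, where m(p) = phi(z)/p, phi is the standard normal density and z is its (1 − p) quantile. So

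bias = rho × [m(p1) − m(p2)] SD.

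The values needed are m(0.4) = 0.966, m(0.5) = 0.798, m(0.6) = 0.644 and m(0.8) = 0.350.

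With 20 fathers per phase and unit SD, the standard error is sqrt(1/20 + 1/20) = 0.316 SD. The rejection rate of a two-sided 5% normal test with no programme effect is Φ(−1.96 + bias/0.316) + Φ(−1.96 − bias/0.316).

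| p1 | p2 | rho | Bias (SD) | Rejection rate |
|---|---|---|---|---|
| 0.6 | 0.6 | any | 0 | 0.050 |
| 0.5 | 0.6 | 0.1 | 0.015 | 0.050 |
| 0.5 | 0.6 | 0.5 | 0.077 | 0.057 |
| 0.5 | 0.8 | 0.3 | 0.134 | 0.071 |
| 0.5 | 0.8 | 0.5 | 0.224 | 0.109 |
| 0.4 | 0.8 | 0.5 | 0.308 | 0.164 |

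For comparison, 80% power at 20 per phase needs a difference of (1.960 + 0.842) × 0.316 = 0.89 SD.

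**5. Reading the table.** An added reason to consent would be expected to raise consent, so p2 exceeds p1 and phase 1 is the more selected group. Whether that flatters or masks the programme depends on the sign of rho. The zero in the top row assumes that the same trait drives consent in both phases. If the offer changes which trait matters, equal consent rates could still hide different fathers.

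**The case against.** The case against is substantial.

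- **The gate is narrow.** A motivated father can have three of the five strategies without enrolling. The article also describes the activities as standard family integrated care already practised at the centres, and it does not say that the materials are refused to others. This stands, and it limits the incentive.
- **Recruitment is controlled.** The criteria are the same in both phases and eligible parents are taken in sequence. This limits selection by the recruiter, but not by the father.
- **Staff teaching.** Because staff are taught between phases to "educate and upskill all clinical NU staff on the study aims, recruitment, phase 1 study findings, and upcoming phase 2 study", a reader might infer that families are approached differently in phase 2. That is speculation: phase 1 also includes introducing the study to the wider staff.
- **Questionnaires are supportive.** The Discussion says they support the qualitative data and that a larger sample would be needed for quantitative inference. So rejection rates are not the main issue, although the interviews come from the same fathers.
- **A refusal log may exist.** An article may leave this to the full protocol, and the sentence on language does not show that nothing else is recorded. This too stands. The point rests on the access rule that the article itself states.

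A reader might also infer that the phases do enrol different fathers and that the contrast is biased in the programme's favour. The article does not support that: it gives no consent, refusal or father data by phase. A larger bias can be produced by assuming no self-selection in phase 1 and strong self-selection in phase 2. That fits poorly with an added reason to consent, and with a phase 1 that already asks for two interviews and repeated questionnaires.

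**Conclusion.** The incentive to consent differs by phase, and the article's own access rule creates the difference. Differential volunteering is therefore a possible confounder of the phase contrast, not a demonstrated bias. Its direction is undetermined and its size may be zero. Under the assumed consent rates and correlations it runs from 0 to about 0.3 SD, mostly below the 0.32 SD standard error. Those inputs are not in the article, so the figures show scale only.

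The first questionnaires, as timed, cannot settle the matter. Nor can it be said that the leaflet or consent wording differs by phase, because those appendices are not shown. The point merits a cheap improvement; it does not invalidate the design.

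**What to change.** 1. Extend footnote a of Table 2 to the booklet or app and the workbook, and align the phase 2 sentence on materials, so that access does not depend on enrolment. There is no concurrent control group to contaminate, apart from any phase 1 family still on the unit.
2. In phase 2, have the first questionnaires completed before materials are handed over where possible. Once the materials are open, some fathers may have them before enrolling, so record both dates.
3. From the eligibility assessment already made for every family, tabulate eligible, approached, declined and enrolled families by phase, with gestation and unit, and show this beside the phase comparison.

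The cost is some extra copies or app access and a simple log, with no added assessments. Consent restricted to the assessments in both phases is not needed, and would not suit phase 2, which also asks parents about the programme.

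Results reports 22 families recruited by October 2023. If the cap of 20 held, at least 22 − 20 = 2 were already in phase 2. Items 1 and 2 can therefore apply only to families still to be recruited; item 3 can be done for both phases as far as records allow.

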### Statistical Analysis

Qualitative data will be imported into dedicated software packages to facilitate analysis including NVivo (Lumivere) and SPSS (SPSS Inc). Interviews will be transcribed, following which the original recordings will be destroyed.

### Interviews and Focus Groups

Data will be uploaded into NVivo to facilitate qualitative data management and thematic analysis. We will use several methods to minimize researcher bias during the study. All interviews will be conducted by 1 person (RR), who will maintain a reflexive diary through the study process. The transcripts will be independently coded by 2 researchers (RR and KG) to find repeated patterns of meaning which provide a detailed understanding of the perspective of the participants [29]. Both researchers will systematically code the data in detail and group them together into broader themes, with themes revisited to ensure that data saturation has been reached. These will then be grouped into broader themes generating a thematic map that will allow us to understand the parents’ experiences in NU. The chief investigator (NA) will have control of the data and will be able to access the audio recordings of the interviews at all times to audit the quality of the interview process. Decision trails and coding trees will be used to ensure that coding and decision-making in data analysis are clear and transparent. Any discrepancies will be discussed with a third person (NA). Verbatim (anonymous) quotes will be shared with the results to allow the reader to determine whether the final themes reflect the data. Finally, the research team and participants will be invited to comment on the emerging or final themes during the data analysis.

### Questionnaires

For descriptive statistics, the median and mode scores of the PSS:NICU, GAD-7, and PHQ-9 will be used to describe the outcome of the questionnaires. For inference analysis, the difference in median for the PSS:NICU, GAD-7, and PHQ-9 at admission, discharge, and 6 weeks postdischarge will be compared between phase 1 and phase 2 using the Mann-Whitney test and the paired 2-tailed *t* test. The data will be checked for outliers and these will be corrected or removed. However, where these outliers are accurate, a nonparametric statistical analysis will be performed. Depending on the data type, missing data will be replaced with mean, median, or mode. In addition, regression and multiple imputations analysis will also be used to impute or generate missing values.

Staff survey questionnaire responses to individual questions will be presented as a percentage of individuals responding yes or no. The percentage of “yes” responses to each question by the staff at the start and end of the study will be compared by paired *t* test.

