**Methods:**

This is a 2-phase study: phase 1 to gather baseline information and phase 2 to assess the impact of enhanced father or partner engagement in FICare on their MH, involving 2 NUs (tertiary and level 2). Enhanced FICare will be developed and introduced (eg, information booklet, workbook, classes, and a father peer-support group) alongside standard FICare practices. Father or partner MH will be assessed with semistructured qualitative interviews and validated questionnaires: Generalized Anxiety Disorder Assessment, Patient Health Questionnaire, and Parental Stressor Scale: Neonatal Intensive Care Unit from NU admission to 6 weeks postdischarge. Mothers will be assessed by focus groups and the same questionnaires. Descriptive statistics and appropriate comparative tests, such as the 2-tailed *t* test, will be used to analyze and compare phase 1 and 2 data. Qualitative data will be coded line by line with the use of NVivo (Lumivero) and thematically analyzed. Simultaneously, systematic reviews (SRs) of fathers’ experiences of FICare and their MH outcomes will be conducted. The study was approved by the National Research Ethics Committee (22/EM/0140) in August 2022. A parent advisory group was formed to advise on the study methodology, materials, involvement of participant parents, and dissemination of study findings.

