#### Sample Size

The sample size of the study is estimated based on qualitative study outcomes. A recent SR of qualitative study demonstrated that to achieve data saturation we need to interview 9 to 17 participants [24]. A focus group of 5 to 7 participants would be enough for in-depth conversations and 2 or more groups would increase the chances of successful data output [25].

In the first and second phases, up to 20 parents will be recruited (until the fathers’ interviews reach data saturation). With a father and mother each, there could be 40 participants per phase. In total, there could be 80 participants in the study.

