### Potential Risk to Participants and Mitigation

Considering the nature of the study, it is unlikely to have any adverse events. However, fathers may feel the additional burden of fulfilling their expected NU obligations alongside their breadwinner role and feelings of guilt for being unable to fulfill the expectations set for them [30,31]. To mitigate this difficulty, there is flexibility in when and to what extent fathers would like to be involved in FICare set at their own pace. The questionnaires and interviews may be emotionally challenging. This is being mitigated by the option to attend peer support sessions run by an appropriately trained professional and all parents will have access to the local neonatal psychologist. Interview frameworks were reviewed by the PAG and neonatal psychologist. A protocol is in place for any participants exhibiting severe MH symptoms through questionnaire responses or other forms of communication. Adverse events will be reported to the chief investigator and local research and development office and follow research and development, protocols with consideration of modification of study procedures if required.

Adverse events in the hospital setting will follow local hospital protocols as well as escalation to study PI with consideration of modification of study procedures if required. The risk of psychological distress resulting from study participation has been minimized with the support of a specialist psychotherapist who reviewed the study design and materials. A protocol is in place for any parents exhibiting severe MH symptoms through questionnaire responses or other forms of communication. We do not anticipate any risks to parents as they are simply being encouraged to participate in standard FICare activities that already occur in the participating centers. There is an emphasis that this should occur at the parents’ pace.

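### The phase effect is stated as a difference in medians, but Mann-Whitney and the t test do not test medians, so estimate and p-value could occasionally disagree (minor)

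*Protocol article*

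**What the plan says.** The Questionnaires section under Methods fixes three things.

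- **Description:** "the median and mode scores of the PSS:NICU, GAD-7, and PHQ-9 will be used to describe the outcome of the questionnaires".
- **Quantity compared:** "the difference in median for the PSS:NICU, GAD-7, and PHQ-9 at admission, discharge, and 6 weeks postdischarge will be compared between phase 1 and phase" two.
- **Tests:** the scores "will be compared between phase 1 and phase 2 using the Mann-Whitney test and the paired 2-tailed" t test. The abstract also gives the t test as its example of a comparative test.

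The section makes no assumption that the two phases have score distributions of the same shape, and it names no test aimed at medians.

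On size, the Sample Size section says "In the first and second phases, up to 20 parents will be recruited". It then counts a father and a mother for each, giving up to 40 participants per phase and 80 in all. A comparison of fathers, or of mothers, therefore has at most 20 per phase.

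On role, the Outcomes section makes all questionnaire scores secondary. The Discussion says that they support the qualitative data and test feasibility, and that a larger sample would be needed to base the study on them.

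**The concern.** The article names both the quantity to be compared and the tests to compare it with, and the two do not match.

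Mann-Whitney takes its reference distribution from the hypothesis that the two phases have the same distribution. What drives the result is whether a score from one phase tends to exceed a score from the other. This becomes a statement about medians only if the distributions differ by a pure shift. A t test concerns means, whether paired or not. (Pairing parents from two phases that enrol different families is a separate fault, and this point does not depend on it.)

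Equal shape cannot be taken for granted here. GAD-7 and PHQ-9 are bounded integer scores (0 to 21 and 0 to 27). Uptake of the programme is also left to each father: "there is flexibility in when and to what extent fathers would like to be involved in FICare". The benefit could therefore vary between fathers, and it could fall mainly on those with high scores. That is a plausible pattern, not one that the article states.

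At stake is how a result is read. If the upper tail shrinks while the middle stays put, the p-value can respond to a change that the reported median difference largely misses. The planned description by median and mode would not show that change either.

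**Working it through.** **1. The article's own figure.** 20 families × 2 parents × 2 phases = 80, as stated. The article gives no alpha, power, effect size or standard deviation for the questionnaires. The two-sided 5% level and all score distributions below are assumptions.

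**2. Can the two quantities part?** Two constructed data sets, 20 scores per phase:

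- *Equal medians, small p.* GAD-7-type scores.
  - Phase 1: 4, 4, 5, 5, 5, six 6s, 12, 13, 14, 14, 15, 16, 17, 18, 19.
  - Phase 2: 0, 0, 0, 1, 1, 1, 1, 2, 2, seven 6s, 7, 7, 7, 8.
  - Both medians are 6, so the difference is 0.
  - Counting pairs in which phase 1 is higher, with ties as one half: U = 5×9 + 6×(9 + 3.5) + 9×20 = 45 + 75 + 180 = 300. U/400 = 0.75, Mann-Whitney p = 0.006.
  - The Hodges-Lehmann shift is 5 points. The means are 9.85 and 3.95, a difference of 5.9.
- *Opposite direction.* One group has eleven 3s and nine 15s (median 3). The other has nine 0s and eleven 8s (median 8). U for the first group = 11×9 + 9×9 + 9×11 = 279 of 400, p = 0.028. The group with the lower median ranks higher.

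These show that disagreement is possible. They say nothing about how often it occurs.

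**3. How often, under upper-tail compression?** Assumed phase 1: PHQ-9-type scores, gamma with shape 2 and scale 4.17, rounded and limited to 0-27, median 7. Assumed phase 2: the same, with each excess above 7 halved. The median stays 7 and the mean falls from 8.3 to 6.9. With 20 per phase:

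| Scenario | Mann-Whitney rejects at 5% |
|---|---|
| Identical distributions (control) | 4.6-4.8% |
| Upper-half excess halved | 7.2-7.9% over repeated runs |
| Spread differs only (gamma shape 6 vs 0.8, both median 7) | 6.8-6.9% |

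The control holds its level, so the excess comes from the mismatch with medians and not from a faulty test.

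**4. Check by hand.** Treat the excess above the median as roughly exponential and ignore ties. Four equally likely cases arise, according to whether each parent lies above or below the median. The probability that the phase 1 score is higher is 1/2 (both below), 1 (only phase 1 above), 0 (only phase 2 above) and 1/(1 + 0.5) = 0.667 (both above). The average is (0.5 + 1 + 0 + 0.667)/4 = 0.542.

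The null standard error of U/400 is √(41/(12×400)) = 0.092. The displacement is 0.042/0.092 = 0.45 standard errors. The rejection probability is about Φ(−1.96 + 0.45) + Φ(−1.96 − 0.45) = 0.066 + 0.008 = 7.4%, in line with the simulation.

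**5. How often would a reader see a median difference of 0 with p<0.05?** In the upper-compression scenario, both events together occurred in 0.00% of runs. Allowing an observed median difference of up to 1 point gives 0.1%.

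**6. Stronger shape changes.** Cutting the upper excess by 60% and stretching the lower half downward 1.8-fold gives Mann-Whitney rejection of 21-24%. Cutting it by 75% and stretching 2.5-fold gives 39-40%. Even there, p<0.05 with an observed median difference of exactly 0 occurred in at most 0.02% and 0.2-0.46% of runs.

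**The case against.** The strongest reply has four parts.

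- **Common shorthand.** Calling Mann-Whitney a comparison of medians is widespread, and under a pure shift nothing is lost. This stands, and it is one reason why the point is minor. The article does not, however, state or argue for a shift.
- **Not false findings about the programme.** In every altered scenario phase 2 scores really are lower, for example a mean of 6.9 against 8.3. The test detects a real difference, and what is wrong is the name given to it. This stands in full.
- **A condensed article.** Effect measures and confidence intervals are commonly left to a fuller document. This also stands, and their absence is not the point. The point is that the quantity and the tests that are stated do not fit each other.
- **Little depends on it.** The primary outcome is assessed by interview, and the study is sized on saturation.

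A reader might infer more: that results of the form *median difference 0, p<0.05* are to be expected, or that the error rate rises to 20-40%. The documents support neither. The first is rare in every scenario tried. The second needs the lower half of the scores to be stretched downward while the median is held fixed, which puts about 20-29% of phase 2 parents at a score of 0, against 0.7% in phase 1. Nothing in the article suggests such a pattern. Flexible uptake does not by itself imply that only high scorers improve. The t-test rates in these scenarios (about 12% under upper compression) add no weight, because they come from an unpaired t test, which the Questionnaires section does not name.

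**Conclusion.** The point holds as a mismatch between a stated effect measure and the stated tests. Under plausible upper-tail compression with equal population medians and 20 parents per phase, Mann-Whitney rejects about 7-8% of the time instead of 5%. This size rests on assumed score distributions, because the article gives none. The practical consequence is that estimate and p-value could occasionally disagree, in size and in extreme cases in direction. A significant Mann-Whitney result should therefore not be worded as a difference in medians. It is not a sign that the tests are invalid or that false claims of benefit would be common. Severity is minor, since the outcomes are secondary and supportive.

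**What to change.** Change the inferential sentence in the Questionnaires section as follows.

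- Use one unpaired, two-sided Mann-Whitney test for each comparison between phases, and drop the paired t test for this purpose.
- Replace the difference in medians with a measure that matches the test, with a 95% confidence interval: the Hodges-Lehmann shift in scale points, or the probability that a phase 2 parent scores lower than a phase 1 parent (ties counted as one half).
- Keep medians as description, with quartiles added so that a change in the upper part of the scores can be seen.
- Do not word a significant Mann-Whitney result as a difference in medians.

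If the difference in medians is truly the target, a median-based method, such as quantile regression or a bootstrap interval for the difference, would also resolve the mismatch.

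The cost is one rewritten sentence and a standard software option, with no new data and no change in sample size. The drawback is that either measure is less familiar to clinical readers than a median difference and needs a line of explanation.
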